
### Quality assurance

To ensure the quality of the consent delivery, all recruitment staff have been certified to consent participants. Certification occurs after peer role playing and practice at the site, with a goal of role playing the informed consent process at least three times before being certified.

To ensure the fidelity to the intervention and quality of the curriculum delivery for both the intervention and control groups, the FHCs (who only deliver lessons to intervention group) and FHLs (who deliver lessons to control group and administer self-report assessments for both intervention and control) complete a knowledge test for each lesson and complete two role plays.

for each lesson before delivering the lesson to a participant. In addition, they are observed in person on a quarterly basis, and all lessons are audio recorded so that a random 10% of recordings can be reviewed and rated for fidelity.

### Quality control of data management

Data assessments are initially checked for quality at the field level. All data are directly entered into an electronic database using the REDCap mobile App on iPads by the FHL, IE, or the participant herself. Data are uploaded at the end of each day to the REDCap web-based database. The data management plan includes quality control at the field level and in Baltimore. Study coordinators follow data verification procedures on a weekly, bi-weekly, and quarterly basis to generate information needed to identify specific errors and missing data. Data are currently being uploaded into a secure, HIPAA-compliant server on a weekly basis by the Baltimore-based coordinator. Data are exported out of REDCap for quality control routines in Stata. All Stata data sets are stored on a JHU secure server. All errors or missing data identified are noted in a log and communicated with study coordinators. The field coordinator creates necessary queries in REDCap that field staff respond to log data corrections.

### Sample size calculation and statistical analysis

Sample size was powered to detect meaningful differences between the intervention (FSN + OSC) and control group (OSC + IPE) across six primary outcomes: 1) percent ever breastfed, 2) percent exclusively breastfed through 6 months of age, 3) mean duration of breastfeeding (at 12 months postpartum), 4) percent ever introduced sugar sweetened beverages at 12, 18 and 24 months, 5) mean score on responsive feeding scale (5-point scale – evaluated at 2, 4, 6, 9, 12, 18 and 24 months postpartum), and 6) mean BMI z-score at 24 months of age. A sample size of 338, or 169 per group, was deemed sufficient to detect meaningful differences across all outcomes, taking into account an estimated 16% loss-to-follow-up at 24 months postpartum (based on the previous FS trial) [54] and ensuring at least 80% power and significance level of 5%. Sample sizes and power were calculated using Stata 13’s power command (two means for continuous variables and two proportions for binary variables) (Table 3). The only exception among the primary outcomes was BMI z-score. Power simulation was conducted using a random draw and random treatment assignment from real site population data. The simulation varied the treatment effect and was run 10,000 times for each treatment effect level from which power was calculated. Simulation was also used to calculate power for moderator analyses. We hypothesize that maternal psychosocial factors, food/water insecurity and constrained physical activity environment will moderate the impact of the intervention on maternal feeding practices and healthy weight knowledge/behaviors. We also hypothesize that food/water insecurity and constrained physical activity could moderate the impact of improved maternal feeding practices and healthy weight behaviors on child diet and physical activity. While we will not have the power to examine interaction terms for all outcomes, we will have > 80% power to detect meaningful difference of differences in breastfeeding duration (48 days) and responsive feeding scales (0.4 to 0.6). The interaction terms for other outcomes will be explored as hypothesis generating to determine trends that would warrant further study with larger samples sizes.

**Table 3 Tab3:** Sample Size Calculations

Outcome Measures	Detectable Differences
% Mothers initiated breastfeeding	14%
% Exclusive breastfeeding through 6 months of age	15%
Mean breastfeeding duration	23 days
% Introduced SSBs	13%
Infant/Toddler Responsive Feeding Scale:	
• Responsive • Forceful • Indulgent • Restrictive • Uninvolved	0.20 points 0.24 points 0.22 points 0.20 points 0.32 points
BMI z-score	0.33 (SDs)

Blood samples are collected from all mothers prior to delivery, and cord blood is collected from all infants at delivery (*N* = 338 mother/infant pairs). Blood samples are also collected from a subset of 72 mother/infant pairs at 6 months postpartum, and 260 infants at 12 months postpartum. Reduced sample sizes at 6 and 12 months postpartum are related to time and budget constraints. These sample sizes will allow us to examine whether mother/infant biologic metrics are correlated at each time point and to build predictive models for infant biologic outcomes. Additionally, *n* = 72 mother/infant pairs with baseline and 6-month follow up will allow us to detect meaningful differences in the related biometric measures by maternal characteristics and/or maternal/infant behaviors (standardized mean detectable differences = 0.68), taking into account 4% loss-to-follow-up at 6 months postpartum (based on previous Family Spirit trials) and ensuring 80% power and significance level of 5% [69]. Finally, a sample size of *n* = 260 infants at 12 months will allow us to detect meaningful between intervention group differences in infant biometric outcomes (standardized mean detectable differences = 0.38), taking into account 16% loss to follow-up at 12 months postpartum and ensuring 80% power and a significance level of 5%.

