### Breastfeeding

Breastfeeding protects against obesity, CVD, and diabetes [31, 32]. National data indicate that less than three-quarters (68.9%) of NA mothers initiate breastfeeding and only a little more than one-third (37.1%) continue through 6 months postpartum [33]. NA mothers have reported lack of understanding of obesity-related benefits of breastfeeding [34]. Additionally, there is an identified need for more research about how breastfeeding education and support may impact uptake of breastfeeding and duration [35].

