## Methods/design

### Trial design

This study is a two-arm randomized controlled trial (RCT) with primary endpoints of parent feeding practices, young children’s diet and PA, and early childhood (0–2 years of age) weight status. Stratified block randomization with a 1:1 allocation is used to ensure equal allocation to intervention and control groups across key maternal baseline characteristics (Fig. 1).

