#### Primary outcomes

Group differences in percentage of mothers who meet breastfeeding and complementary feeding recommendations and percentage of mothers who introduce SSBs over time as assessed by the Child Feeding Assessment. From 2 weeks to 24 months pp., mothers are asked questions from an adapted version of the Pre-School-Aged Beverage Intake Questionnaire (BEVQ-15) in addition to items developed by the study team and based on previous studies conducted by the co-investigators. The assessment will be used to assess feeding practices, duration of exclusive and non-exclusive breastfeeding, timing of introduction of complementary foods and types of first foods, and introduction of SSBs.Group differences in mean scores for infant feeding style subscales assessed using the Infant Feeding Behavior Questionnaire, which asks mothers to indicate how often they engage in specific feeding behaviors to assess maternal feeding styles from 2 month to 12 months pp. There are five subscales that are used to assess maternal feeding style: Responsive, Forceful, Restrictive, Indulgent, and Uninvolved. There is no total scale score. The assessment is valid and reliable. This 24-item scale is scored with a 3-point Likert scale. A mean score is calculated for each subscale, with a range of 0 to 2. The range of the 3-point Likert scale is as follows: 0 (never), 1 (sometimes), 2 (always). Higher scores reflect higher levels of feeding style indicated by a given subscale.Group differences in in mean scores for toddler feeding style subscales assessed using the Toddler Feeding Behavior Questionnaire, which asks mothers to indicate how often they engage in specific feeding behaviors to assess maternal feeding styles at 24 months pp. There are five subscales that are used to assess maternal feeding style: Responsive, Forceful, Restrictive, Indulgent, and Uninvolved. There is no total scale score. The assessment is valid and reliable. This 27-item scale is scored with a 3-point Likert scale. A mean score is calculated for each subscale, with a range of 0 to 2. The range of the 3-point Likert scale is as follows: 0 (never), 1 (sometimes), 2 (always). Higher scores reflect higher levels of feeding style indicated by a given subscale.Group differences in children’s consumption of fruit and vegetable intake from SSBs, snacks, and desserts over time as assessed by the USDA Household Food Security Survey. From 6 months to 24 months pp., mothers are asked questions about her child’s fruit and vegetable consumption beginning at 6 months postpartum and at all subsequent time points. These items have been added to a standardized 18-item USDA food security survey, the U.S. Household Food Security Survey, that measures household food security. Fruit and vegetable consumption will be measured by asking mothers how much and how often her child eats fruits and vegetables and whether she feels she is able to provide her child with the fruits and vegetables he or she needs. To obtain weekly fruit and vegetable servings consumption, the number of times per week fruits or vegetables are consumed will be multiplied by the number of servings consumed each time. Serving size will be age adjusted.Group differences in children’s PA levels as assessed by accelerometry. At 18- and 24-months pp., children’s PA will be measured objectively using accelerometry. We will use the Actical accelerometer, a small waterproof device (28x27x10mm) weighing 17 g, which is omnidirectional (sensing motion in all planes) and integrates the degree and intensity of motion. We will use procedures co-investigators have used successfully in previous studies of young adolescents, toddlers and their mothers, placing the accelerometer on the non-dominant ankle with a non-removable, reinforced hospital band worn next to the skin, under socks, for 7 consecutive days. Accelerometers will be attached on the day of the 18- and 24-month assessment battery and removed one week later. Data will be collected in 1-min epochs. The time-stamped data will be examined. Summary statistics will include average and total activity counts and minutes in MVPA.Group differences in children’s reported PA, screen time and other sedentary activities over time as assessed by the Child Physical Activity Assessment from 2 months to 24 months pp. This 14-item self-report assessment includes questions about tummy time, crawling, walking, sedentary behavior and screen time for infants and toddlers. Questions were compiled based on a body of literature related to assessing infant/toddler physical activity.Group differences in children’s mean BMI z-scores over time (2 weeks to 24 months pp) as assessed through child weight and length measurements over time. Description: Child weight (to the nearest ounce) and recumbent length (to the nearest 1/8 in.) are measured using a digital scale and a recumbent measuring board (in accordance with IHS guidelines). All measurements will be taken in triplicate, removing the most disparate measurement, and averaging the remaining two. Averages will be used to calculate BMI z-scores using age- and sex-specific WHO Child Growth Standards.

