#### Primary aims analysis

We will conduct intent-to-treat analyses to estimate effects of the FSN + OSC intervention compared to the OSC + IPE control condition on early childhood obesity and related risk factors. Separately, we will examine the effects of intervention dose and conduct a “completer analyses” on subjects receiving minimum intervention dose (> 50% of lessons). Analyses will be adjusted for multiple comparisons using Bonferonni corrections.

Demographic and outcome variable distributions will be examined to assess whether comparability between intervention groups at baseline was achieved through randomization. For time discrete outcome measures, t- tests or chi-square tests will be used to test whether the intervention impacted each outcome in unadjusted analyses. Multiple linear or logistic regression will be used to test the impact of the intervention on each outcome, controlling for baseline demographic characteristics where necessary and examining potential moderators in secondary analyses. For time varying outcome measures we will examine the impact of the intervention by analyzing between group differences at each time point using t-tests and multiple regression analyses. For those outcomes with sufficient power, multi-level mixed-effects regression with a random effect at the individual level and appropriate variance structures, and an interaction term for treatment x child age will be used to examine change over the course of the intervention period for the intervention and control groups.

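### Mean breastfeeding duration to 12 months is a powered primary outcome with loss expected, but the methods named for it cannot use the partial duration of a mother lost while still breastfeeding

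*Protocol article*

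**What the plan says.** The sample-size section of the protocol article lists six powered primary outcomes, the third being "mean duration of breastfeeding (at 12 months postpartum"). Power came from Stata's two-means and two-proportions commands, BMI z-score being the only exception, so duration was powered as a comparison of two means. Table 3 gives its detectable difference as 23 days. On the total, "A sample size of 338, or 169 per group, was deemed sufficient to detect meaningful differences across all outcomes", allowing for 16% loss at 24 months and "ensuring at least 80% power and significance level of 5" per cent.

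Under Primary outcomes, the Child Feeding Assessment, asked from 2 weeks to 24 months, is the source for "duration of exclusive and non-exclusive breastfeeding". Duration is therefore built up from repeated visits.

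Under Primary aims analysis, for outcomes that do not vary over time, "t- tests or chi-square tests will be used to test whether the intervention impacted each outcome in unadjusted analyses". Multiple linear or logistic regression follows, and mixed-effects models are reserved for change over time. The analysis is called intent-to-treat. No time-to-event method, censoring rule or restricted mean is named.

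The biomarker calculations in the sample-size section use 4% loss at 6 months and, at the horizon that matters here, "taking into account 16% loss to follow-up at 12 months postpartum".

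**The concern.** A mother who leaves at 4 months while breastfeeding tells us only that her duration was at least 4 months. A t-test or linear regression needs one complete number per mother. Without imputation, three options remain:

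- **Last contact:** count her last contact as weaning, which shortens her duration.
- **Selective exclusion:** drop only mothers whose stopping date is unknown, which removes long breastfeeders.
- **Drop all leavers:** this discards observed time and is valid only if leaving is unrelated to feeding.

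The protocol chooses none of these. They can give different answers on a primary outcome, and choosing after the data are seen would leave the estimate open to that choice. Contact differs by arm (36 planned FSN lessons against 8 control lessons), so unequal loss is possible, although no figure in the document shows it.

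**Working it through.** **1. The plan's own figure.** Evaluable mothers per arm: 169 × 0.84 = 142. The standardised detectable difference, taking 5% as two-sided, is (1.960 + 0.842) × √(2/142) = 0.332. The 23 days then implies an SD of 23/0.332 = 69 days. No SD is stated, so 23 days cannot be checked independently.

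**2. Inputs for an illustration.**
- From the document (Background, Breastfeeding; national figures): 68.9% initiate and "only a little more than one-third (37.1%) continue through 6 months postpartum". These serve as control rates.
- Assumed: exponential weaning; FSN initiation of 75% with a 20% lower stopping hazard; in steps 4 and 5, loss spread evenly over 365 days and unrelated to feeding.

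**3. True means to 365 days.** Control hazard: ln(0.689/0.371)/182.5 = 0.003392 per day. FSN hazard: 0.8 × 0.003392 = 0.002714. With starting share p and hazard λ, the restricted mean is p(1 − e^(−365λ))/λ.
- Control: 0.689 × 0.7100/0.003392 = 144.2 days.
- FSN: 0.75 × 0.6286/0.002714 = 173.7 days.
- True difference: 29.5 days.

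**4. Last contact taken as weaning.** A lost mother's expected recorded duration is (p/λ) × [1 − (1 − e^(−365λ))/(365λ)], which is 86.6 days in control and 101.0 in FSN. The shortfalls per lost mother are 57.6 and 72.8 days. Multiply each by that arm's loss:

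| Loss, control / FSN | Control mean | FSN mean | Difference | Error |
|---|---|---|---|---|
| 16% / 16% | 135.0 | 162.1 | 27.1 | −2.4 |
| 24% / 8% | 130.4 | 167.9 | 37.5 | +8.0 |
| 8% / 24% | 139.6 | 156.3 | 16.7 | −12.9 |
| 8% / 8% | 139.6 | 167.9 | 28.3 | −1.2 |

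At 16% equal loss the control mean alone falls by about 9 days, but most of this cancels in the contrast.

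**5. Excluding only mothers lost while breastfeeding.** With loss d, this is (mean − d·E[X²]/365)/(1 − d·q). Here X is duration capped at 365 days, and q is the chance that a leaver is still breastfeeding: 0.395 in control, 0.476 in FSN. E[X²]/365 is 115.2 and 145.5. The differences are 28.6 (16/16), 39.7 (24/8), 17.3 (8/24) and 29.1 (8/8), so errors of −0.9, +10.2, −12.2 and −0.4 days.

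**6. Dropping every leaver.** When loss is unrelated to feeding this is unbiased, equal or not. Simulation under these assumptions gave 29.2 to 29.6 days across 16/16, 24/8 and 8/24. The price is falling from 169 to 142 per arm. At 16% loss the simulated standard error was 18.1 days, against 16.9 for Kaplan-Meier (16.9/18.1 = 0.93).

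It fails when loss depends on weaning. As an extreme case, let all loss fall on mothers who had weaned or never started. Mothers still breastfeeding at 365 days are 20.0% of control and 27.9% of FSN. They contribute 72.9 and 101.7 days to the arm means; the rest contribute 71.3 and 72.1. With overall loss of 24% in control and 8% in FSN:
- Control loss among the weaned: 0.24/0.800 = 0.300. Completer mean: (72.9 + 0.700 × 71.3)/0.76 = 161.6.
- FSN loss among the weaned: 0.08/0.721 = 0.111. Completer mean: (101.7 + 0.889 × 72.1)/0.92 = 180.2.
- Difference: 18.5 days. The reverse split gives 197.1 − 149.0 = 48.0, and equal 16% loss gives 33.1, all against a true 29.5.

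In this case nobody is censored while breastfeeding, so Kaplan-Meier returns the true value.

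**7. Kaplan-Meier restricted mean.** In simulation with loss unrelated to feeding it gave 29.2 to 29.7 days in every equal and unequal scenario. A second simulation with a true 23-day gain gave 22.6 to 23.2.

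**The case against.** The strongest reply is that the protocol never says lost mothers are miscounted or dropped. It does not tie the t-test to duration by name, and a statistical analysis plan not shown could impute the missing durations; a t-test on imputed values would be consistent with the text. That stands: a reader might infer that the plan fixes a biased handling rule, and the document does not support that. It does fix a method family with no place for a partial duration, on an outcome where partial durations are expected.

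A reader might also infer that a 12-month mean is the wrong target. It is not. For mothers followed to 12 months it is fully observed and is already a restricted mean.

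Other points also stand:
- The 9-day shortfall is in one arm's mean, not in the treatment contrast.
- Dropping all leavers is unbiased if loss is unrelated to feeding.
- The 24/8 split comes from no passage. Both arms share the assessment schedule, gift cards and transport help.
- The 16% at 12 months belongs to the biomarker sample. Primary-outcome loss is 16% at 24 months, so 12-month loss may be lower. Even loss over the year also puts 8% by 6 months, where the biomarker calculation uses 4%.
- Feeding is asked again at 18 and 24 months, so a missed 12-month visit need not lose the duration.
- Kaplan-Meier also needs censoring to be independent of weaning among mothers still breastfeeding.

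**Conclusion.** The point holds as a mismatch between outcome and named method, not as a demonstrated bias. With equal loss unrelated to feeding, the error in the between-arm difference is about 1 to 3 days, or none if all leavers are dropped at the cost of sample size. With 24% against 8% loss, last-contact or selective exclusion errs by about 8 to 13 days in either direction, a third to over half of the 23-day detectable difference. Dropping all leavers can err by a similar amount or more if loss follows weaning and differs by arm.

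The sizes rest on national initiation and 6-month rates, exponential weaning, an assumed FSN effect and assumed loss patterns. Under these rates the SD of control duration is about 146 days, about twice the 69 implied by Table 3. If durations in these communities are less spread out, the errors in days may differ. Direction and size in the actual trial are unknown. The change should be made because it is cheap and keeps the same target.

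**What to change.** In the sample-size section and under Primary aims analysis, define this outcome as restricted mean breastfeeding time to 365 days: the area under each arm's Kaplan-Meier curve, with non-initiators at 0 and mothers lost while breastfeeding censored at last contact. Mothers lost after weaning keep their reported duration. Report and test the between-arm difference in days, adjusting for covariates by pseudo-values or restricted-mean regression. Add a sensitivity analysis in which mothers lost while breastfeeding are taken to wean at last contact, because the primary analysis relies on independent censoring while breastfeeding. Fix this before anyone sees outcome data by arm.

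The cost is a few sentences and a few lines of code. No extra data are needed, and the result remains a difference in days, so Table 3 keeps its metric.

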### Data collection time points

Our mixed-methods assessment includes maternal self-reports and interviews administered using Research Electronic Data Capture (REDCap) tools hosted at Johns Hopkins University, observations (including maternal/infant anthropometric measurements, infant accelerometry, and home safety assessments), maternal/infant medical chart reviews and maternal/infant blood sample collection (Table 2). REDCap is a secure, HIPAA compliant, web-based application designed to support data capture for research studies. It provides 1) an intuitive interface for validated entry; 2) audit trails for tracking data manipulation and export procedures; 3) automated export procedures for seamless data downloads to common statistical packages; and 4) procedures for importing data from external sources [68].

**Table 2 Tab2:** List of Evaluation Measures

		Pregnancy		Postpartum							
		Baseline	36 weeks gestation	2 weeks post-partum (pp)	2* months pp	4 months pp	6* months pp	9 months pp	12* months pp	18* months pp	24* months pp
Self-Report Interviews											
1. Maternal Demographics	15 min	X	X	X	X		X		X		X
2. Child Feeding Assessment [70]	10–20 min			X	X	X	X	X	X	X	X
3. Maternal Beverage Intake Questionnaire [70]	5 min	X	X		X		X		X	X	X
4. U.S. Household Food Security Survey [71]	3–10 min	X			X		X		X	X	X
5. Brief Infant Sleep Questionnaire (BISQ) [72]	5 min				X		X		X	X	X
Self-Reports											
6. Current Eating Environment Assessment	5 min				X		X		X		X
7. Infant Responsive Feeding Scale [73]	5 min				X		X		X		
8. Toddler Responsive Feeding Scale [73]	5 min										X
9. Baby Eating Behavior Questionnaire [74]	5 min						X				
10. Children’s Eating Behavior Questionnaire – Toddler [75]	5 min								X		
11. Perceptions of Growth Scale [76]	3 min				X		X		X		X
12. Child Physical Activity Assessment	5 min				X	X	X	X	X	X	X
13. Knowledge Questionnaire - Maternal Nutrition, Feeding and Physical Activity Practices	10 min	X			X		X		X	X	X
14. Water Availability Assessment [77]	5 min	X			X		X		X		X
15. Perceived Stress Scale [78, 79]	3 min	X			X		X		X	X	X
16. Centers for Epidemiologic Studies Depression Scale-Revised (CESDR-10) [80]	5 min	X	X	X	X		X		X	X	X
17. Alcohol, Smoking and Substance Involvement Screening Test (ASSIST) [81, 82]	5 min	X							X		X
18. Mastery Scale [83, 84]	5 min	X			X		X		X		X
19. Infant Temperament [76]	3 min				X	X	X	X			
20. Brief Infant Toddler Social Emotional Assessment (BITSEA) [85]	10 min								X	X	X

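### The power section gives the responsive-feeding outcome a 5-point scale and seven visits, but the trial scores it 0–2 at four visits; the detectable differences in points need restating

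*Protocol article*

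**What the plan says.** The section on sample size and statistical analysis in the Protocol article lists six primary outcomes used for power. The fifth is the "mean score on responsive feeding scale (5-point scale", which is "evaluated at 2, 4, 6, 9, 12, 18 and 24 months postpartum".

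The Primary outcomes section describes two questionnaires for maternal feeding style, one for infants (2 to 12 months) and one for toddlers (24 months). Of the infant form it says "This 24-item scale is scored with a 3-point Likert scale", and of the toddler form "This 27-item scale is scored with a 3-point Likert scale". For both: "A mean score is calculated for each subscale, with a range of 0 to 2". There are five subscales and no total score.

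Table 2 (Data collection time points) marks the infant feeding scale at 2, 6 and 12 months and the toddler scale at 24 months. Neither row is marked at 4, 9 or 18 months.

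Table 3, under one infant/toddler heading, gives detectable differences for Responsive, Forceful, Indulgent, Restrictive and Uninvolved of "0.20 points 0.24 points 0.22 points 0.20 points 0.32 points". It states neither the SDs nor the range of the score. The text adds that moderator analyses have more than 80% power for a difference of differences of 0.4 to 0.6 on these scales.

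**The concern.** The two descriptions cannot both be true of the same endpoint. A detectable difference in raw points means something only on a known scale: 0.32 points is 16% of a range of 2 but 8% of a range of 4. Five of the ten rows in Table 3 are in such points. If they were worked out on a 5-point scale, a reader who sets an observed 0–2 difference beside Table 3 uses the wrong yardstick and misjudges how sensitive the trial was. The moderator figure may carry the same problem. The visits also disagree: the power section names three (4, 9 and 18 months) at which Table 2 collects no feeding-style data.

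**Working it through.** **Inputs.** From the sample-size section: 169 per group, 16% loss, at least 80% power, 5% significance, and a two-means comparison for continuous outcomes. From Table 3: 0.20, 0.24, 0.22, 0.20 and 0.32 points. From Primary outcomes: score range 0 to 2. Two-sided testing is assumed, because the article does not state sidedness. The feeding scales named in Tables 2 and 3 are taken to be the questionnaires in Primary outcomes; the five subscale names in Table 3 match.

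**1. Evaluable numbers.** 169 × (1 − 0.16) = 141.96, so 142 per arm.

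**2. Standardised detectable difference.** (1.960 + 0.842) × √(2/142) = 0.3325 SD (0.334 with the noncentral t). This agrees with the 0.33 SD that Table 3 gives for BMI z-score, although that row was obtained by simulation.

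**3. Check of these settings on two other rows.** The article's background rates are assumed as control rates.
- Breastfeeding initiation, 68.9% against 82.9% (14 points): null SE 0.0508, alternative SE 0.0501; (0.14 − 1.96 × 0.0508)/0.0501 = 0.81, power about 79%.
- SSB introduction, 87% against 74% (13 points): null SE 0.0470, alternative SE 0.0464; (0.13 − 1.96 × 0.0470)/0.0464 = 0.82, power about 79%.

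So 142 per arm at about 80% power is a fair reading of how Table 3 was built.

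**4. Implied SDs.** The feeding rows cannot be reproduced directly, because no SDs are given. Solving back, SD = points / 0.3325:

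| Subscale | Points | Implied SD |
|---|---|---|
| Responsive | 0.20 | 0.60 |
| Forceful | 0.24 | 0.72 |
| Indulgent | 0.22 | 0.66 |
| Restrictive | 0.20 | 0.60 |
| Uninvolved | 0.32 | 0.96 |

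**5. Comparison with the 0–2 range.** A variable on 0 to 2 with mean m has SD at most √(m(2 − m)), which peaks at 1.0 when m = 1. An SD of 0.96 requires m = 1 ± √(1 − 0.96²) = 0.72 to 1.28. With mean 1 and all other mothers at 1, it requires 0.96² = 92% of mothers to score exactly 0 or 2. Even a single item answered evenly across 0, 1 and 2 has an SD of only √(2/3) = 0.82, and an average over several items is normally less variable. On a range four units wide the maximum SD is 2, and 0.96 is unremarkable.

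**6. Sensitivity.** At 90% power the standardised difference is (1.960 + 1.282) × √(2/142) = 0.385, and the Uninvolved SD is 0.32/0.385 = 0.83, still very high for 0–2. With no dropout (169 per arm, 0.305 SD) it is 1.05, which is impossible on 0–2.

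**7. The rows on a 0–2 score.** The detectable difference is 0.3325 × SD. For assumed SDs of 0.3, 0.5 and 0.6 it is 0.10, 0.17 and 0.20 points. If the implied SDs came from a scale four units wide and shrink in proportion, the five rows become 0.10, 0.12, 0.11, 0.10 and 0.16. With SDs of 0.3 to 0.5, the printed 0.32 would be an effect of 1.07 to 0.64 SD.

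**8. Visits.** Power section: 2, 4, 6, 9, 12, 18 and 24 months (seven). Table 2 and Primary outcomes: infant form at 2, 6 and 12, toddler form at 24 (four). A two-means calculation compares groups at one time point, so this count does not affect steps 2 to 7.

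**9. Moderator figure.** With evenly split subgroups (71 per cell), the variance of a difference of differences is 4σ²/71 against 2σ²/142 for the main effect. The ratio is 4, so the detectable difference doubles. Twice 0.20 to 0.32 is 0.40 to 0.64, close to the stated 0.4 to 0.6. Breastfeeding duration shows the same pattern (48 days against 23). This suggests a common scale but does not prove it.

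**The case against.** The strongest reply is that this is a descriptive slip without consequence. The label may be a confusion with the five subscales. No SDs are published, so nobody can show that the points were computed on another scale. Four of the five implied SDs (0.60 to 0.72) are possible on 0–2. Because the article promises at least 80% power, the implied SDs are strictly upper bounds.

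Much of this stands. That the rows come from a different scale is an inference, and it rests mainly on Uninvolved. What does not stand is that a slip would account for everything: if the label alone were wrong, the Uninvolved row would still need an SD that a 0–2 multi-item mean would hardly show, even at 90% power.

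A reader might infer several stronger things that the article does not support:
- **That the trial is too small for this outcome.** About 0.33 SD is detectable with 142 per arm whatever the units. Under proportional rescaling the detectable raw difference gets smaller.
- **That the wrong visit list or the use of two forms invalidates Table 3.** The calculation uses one time point, and the table heading already covers both forms.
- **That the infant and toddler forms are pooled as one repeated measure.** Primary outcomes lists them separately, and no section says they will be combined.
- **That the 0.4 to 0.6 figure is wrong.** It came from a simulation whose inputs are not given, so it is affected only if it was run on the 5-point scale.

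**Conclusion.** The point holds as an internal inconsistency about a primary outcome. The score range and the visits in the power section contradict Primary outcomes and Table 2. The range contradiction leaves the five feeding rows of Table 3 without a clear scale, and the Uninvolved row (implied SD 0.96 against a ceiling of 1.0) is not credible on the score the trial will use. The visit contradiction is separate and has no numerical effect.

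The implied SDs rest on two-sided 5% alpha, 16% loss and power at or near 80%. The evidence points to a wider scale but cannot settle it while the SDs are unpublished. Neither the sample size nor the choice of test is called into question; what fails is the use of the printed points as a benchmark for a 0–2 result.

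**What to change.** 1. In the sample-size section, describe the outcome as subscale means from 0 to 2, with visits at 2, 6 and 12 months (infant form) and 24 months (toddler form), so that it agrees with Primary outcomes and Table 2.
2. Recompute the five feeding rows of Table 3 with SDs on the 0–2 score and print those SDs, or give the rows as 0.33 SD.
3. Check which scale the simulation behind the 0.4 to 0.6 difference of differences used, and restate that figure if it was the 5-point scale.

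The cost is wording and recalculation. Sample size, data collection and analysis stay as they are.
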